## II. Research project

1. Planned start for the study: 01/01/2008 (information gathering: 01/07/08) // expected end: 31/12/2010

Length of participation in the study for every single person: 12 months, 3 weeks

2. **Abstract of the project** (*maximum of 1.5 pages*):

**Objective.** The objectives of the present project are the development of a specific interprofessional rehabilitation program to promote active self-management of chronic non-specific low back pain, as well as to compare its effectiveness with the current multidisciplinary orthopaedic rehabilitation.

**Research questions.** The primary research question refers to the effectiveness of the interprofessional rehabilitation program compared to the multidisciplinary orthopaedic rehabilitation. The focus is directed on factors that relate to active self-management, e.g. self-reported functional ability, pain related cognitions, physical activity. *Primary hypothesis:* Adults with chronic non-specific low back pain who participate in an interprofessional rehabilitation program will show significantly improved functional ability 12 months after completion of the program in comparison to adults with chronic non-specific low back pain who participate in the standard multidisciplinary orthopaedic rehabilitation. Secondary hypotheses refer to mechanisms of action of the interprofessional rehabilitation program and its effectiveness regarding important risk factors for the development of chronic non-specific low back pain (Yellow Flags).

**Study design/ methods.** A multicentre prospective quasi-experimental control group design with three time points of measurement will be performed. Temporal sampling with consecutive inclusion of adults with chronic non-specific low back pain are first assigned to a control condition (usual care; n = 294), and after subsequent implementation of the interprofessional rehabilitation program, to an intervention condition (interprofessional rehabilitation, n = 294). To evaluate the effectiveness data of participant are recorded at baseline, discharge, and 12 months.

**Description of the interventions.** The central objective of inpatient multidisciplinary orthopedic rehabilitation (MOR) (control group) is to improve functional health with the main focus on restoring and improving work ability. A MOR lasts on 23 days with a total extent of therapy of 48 hours on average. MOR is provided by a multiprofessional team consisting of physicians, psychologists, sport therapists, physiotherapists, occupational therapists, masseurs, social workers, dieticians and nurses. The interventions are carried out mainly in open groups. Multidisciplinary rehabilitation includes interventions from the physical and psychological dimensions: health education, exercise therapy back school,

physical treatments, psychological interventions in groups and individual counselling, as well as rehabilitation/social counselling.

The intervention group consists of an interprofessional and interdisciplinary inpatient rehabilitation program with a biopsychosocial approach. The program is matched to the MOR with respect to the total duration and total extent of therapy, the included professions and the interventions dimensions (physical, psychological). This program, that is based on existing preliminary work (AG Rehabilitation, 2006), is carried out on twelve days during a three-week rehabilitation. The overall objective of PASTOR is the development of active self-management of chronic non-specific low back pain. The program covers six interprofessional therapy modules with sessions of 30 to 90 minutes in duration: Education about low back pain (ELBP), Behavioural exercise therapy 1 (BET 1), Behavioural exercise therapy 2 (BET 2), Coping with pain (CWP), Relaxation (R), and Workplace related information (WRI).

The differences between interprofessional rehabilitation and multidisciplinary orthopedic rehabilitation are characterized by, a) an integrative combination of profession related modules within a comprehensive and consistent treatment approach, b) an interprofessional and collaborative teamwork based on profession related modules, c) the use of standardized methods, media and materials by all professions in the therapeutic team d) a highly structured and detailed manual for the entire treatment process. The modules are carried in fixed groups with eight to twelve participants.

**Outcomes.** Primary outcome is the level of functional ability 12 months after the end of inpatient rehabilitation measured by the Hannover Functional Ability Questionnaire (FFbH-R). Secondary outcome measures include pain-related cognitions, emotions and behaviour, pain intensity, physical activity, health-related quality of life, time off work and medical visits due to low back pain during the last six month.

**Sample.** N=588; Participants with chronic non-specific low back pain with the following assignment diagnoses M54.4 – M54.9 as well as M51.2 – M51.9 and M53.8 – M53.9 according to ICD-10.

**Sample Size and Power Calculation.** Sample power (Software: G-Power 3.0) concerning the primary outcome is approximated for an analysis of covariance at t3 with a small effect size of Cohen's  $d=0.3$ , a 2-sided  $\alpha=0.05$  and a test power of  $1-\beta=0.8$ . This approximation results in a sample size of at least 352 participants with complete data for both study groups ( $n=176$  per group). Anticipating a dropout rate of 40%, it is necessary to include 588 participants ( $n=294$  per group).

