**c. In your opinion, why is the potential risk defensible in relation to the expected benefit?**

Not applicable.

d. Is there an evaluation of interim findings to recognize a trend?

☐ Yes ☒ No

e. Have been criteria defined that would lead to a change or termination of the study.

☐ Yes, which? ☒ No

11. In case of clinical testings according to MPG (**not applicable**)

12. a) Is cooperation with a statistician intended?? ☐ Yes ☒ No

b) What statistical methods will be used?

The data analysis follows the usual standards in the evaluation of quasi-experimental control group design. To assess the long term treatment effect of interprofessional rehabilitation against multidisciplinary orthopedic rehabilitation, t-test or analysis of covariance (ANCOVA) respectively of functional ability measured with the FFbH-R at the 12-month follow-up will be used, adjusted for baseline differences, as primary analysis. Further possible baseline differences between both study groups in secondary variables (e.g. socio-demographic, medical) will be also addresses via regression analyses or analysis of covariance (Vickers, 2005). The data analyses will be supported by the methodology consulting of the Department of Medical Psychology, Medical Sociology, and Rehabilitation Sciences Würzburg.

13. a) Is this a multi-centre study (i.e. a study carried out by one single study plan but in different study centres and therefore carried out by different examiners)?

☒ Yes ☐ No

b) Have there been/Are there other places that carry out studies with the same or similar design?/ ☒ Yes, where? ☐ No

Effectiveness studies concerning medical rehabilitation or patient education programs implemented in medical rehabilitation about chronic low back pain (i.a. Bandemer-Greulich et al., 2008; Bosse et al., 2007; Greitemann et al., 2006; Mehnert et al., 2007; Schwarz et al., 2007; Metaanalyse: Hüppe & Raspe, 2003, 2005).

14. Who initiated the study?

[name]. [name] (University Erlangen), Dr. phil. [name] (University Würzburg) and Dr. med. [name] (German Society for Orthopedics and Orthopedic Surgery DGOOC, Asklepios Rehabilitation centre Schaufling)

15. Who funds the study? (*Please indicate if you applied for funding at a third, non-public party. If yes, which amount?*)

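### Fixed therapy groups of 8 to 12 in the intervention arm are ignored in the power calculation and the stated primary test, so with any positive within-group correlation the error rate exceeds 5% and power falls below 80%

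*Protocol*

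**What the plan says.** All references are to the Protocol.

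- **Delivery, intervention arm** (II.2, Description of the interventions): "The modules are carried in fixed groups with eight to twelve participants". Section II.3 repeats this and presents it as one of the ways the programme departs from usual routine. The modules are spread over twelve days of a three-week inpatient stay.
- **Delivery, control arm** (II.2, same paragraph block): "The interventions are carried out mainly in open groups".
- **Sample size** (II.2, Sample Size and Power Calculation): "Sample power (Software: G-Power 3.0) concerning the primary outcome is approximated for an analysis of covariance at t3". The inputs are d = 0.3, two-sided alpha 0.05 and power 0.8. The result is 176 per group with complete data, raised to 294 per group (588 in total) for 40% dropout.
- **Primary analysis** (II.12 b): "t-test or analysis of covariance (ANCOVA) respectively of functional ability measured with the FFbH-R at the 12-month follow-up will be used", with adjustment for baseline differences.

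Neither the sample size paragraph nor II.12 b mentions an ICC, a design effect or a term for therapy group.

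**The concern.** Intervention participants go through the programme in one closed group, with shared sessions and shared peers. Their outcomes may therefore resemble each other more than those of participants from different groups. Control participants mostly have no such fixed membership. This is a partially nested design, clustered in one arm and essentially not in the other.

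A t-test or ANCOVA that treats every participant as independent omits the between-group variance in the intervention arm. At stake are a primary confidence interval that is too narrow, a nominal 5% test that rejects more often than 5%, and a power statement that holds only if the within-group correlation is zero.

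There is also a practical risk. The centres run the whole questionnaire survey and the research institutes receive only anonymous data (II.2, Data acquisition). The assignment lists stay in the centres and are deleted at the end (II.4). The text shown provides for no therapy-group code in the data. If none is attached, the clustering may not be recoverable later.

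**Working it through.** **1. Reproduce the plan's own figure.** For a two-sample t-test with d = 0.3, two-sided alpha 0.05 and n per group, the noncentrality is 0.3 × √(n/2).

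- n = 176: noncentrality 2.814, power 0.801. n = 175: power 0.799. So 176 is the smallest n that reaches 80%.
- As an ANCOVA F-test with f = 0.15, one covariate and N = 352, power is also 0.801.
- 176 / 0.6 = 293.3, rounded up to 294.

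The arithmetic is right. The result is the independent-observations figure plus dropout, with nothing added for clustering.

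**2. Cluster size.** 294 participants in groups of 8 to 12 form about 25 to 37 groups (294/12 = 24.5; 294/8 = 36.75). For the main case, assume groups of 10 made up entirely of study participants. With 40% loss, m = 10 × 0.6 = 6 analysed per group.

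**3. Formulas** (clustering in the intervention arm only).

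- Design effect in that arm: DE = 1 + (m − 1) × ICC.
- True variance of the difference relative to the independence variance: R = (1 + DE)/2.
- Actual two-sided type I error of the unadjusted test: 2 × [1 − Φ(1.96/√R)].
- Power of a test with the correct standard error: noncentral t with noncentrality 2.814/√R.

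**4. Results for m = 6.** The ICC values are assumptions, because the protocol gives none.

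| ICC | DE | R | True SE / computed SE | Type I error | Power at d = 0.3 |
|---|---|---|---|---|---|
| 0 | 1.00 | 1.000 | 1.000 | 0.050 | 80% |
| 0.01 | 1.05 | 1.025 | 1.012 | 0.053 | 79% |
| 0.05 | 1.25 | 1.125 | 1.061 | 0.065 | 75% |
| 0.10 | 1.50 | 1.250 | 1.118 | 0.080 | 71% |

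**5. Sensitivity to m.** Groups of 12 with 40% loss (m = 7.2) at ICC 0.10 give R = 1.31, type I error 0.087 and power 69%. Non-study patients in the groups would lower m; less dropout would raise it. The power column uses 350 degrees of freedom. With an illustrative 60, to reflect the limited number of groups, power falls by about one more percentage point.

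**6. Possible offset from baseline adjustment.** If d = 0.3 is in raw SD units, ANCOVA with baseline-outcome correlation r multiplies the variance by 1 − r². Treating the ICC as unchanged by adjustment, the power loss is cancelled when (1 − r²) × R = 1, that is r = √(1 − 1/R).

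- ICC 0.05: r = √(1 − 1/1.125) = 0.33.
- ICC 0.10: r = √(1 − 1/1.25) = 0.45.

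This does not help the type I error. That depends on R, the ratio of the true to the assumed variance, and baseline adjustment shrinks both.

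**The case against.** **The size depends wholly on an ICC that the protocol does not give.** This stands. At ICC 0.01 the consequence is practically nil, and with m = 6 the type I error passes 0.06 only once the ICC is above about 0.034. Section II.3 also stresses standardised delivery with little variation in treatment between individuals, which argues for a low ICC. It does not show a zero ICC, because shared group dynamics remain.

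**Details of the model belong in a SAP, which is not shown.** This stands in part. A SAP could add a group term, and random effects or degrees-of-freedom methods need not be in a protocol. But the power figure is fixed in the protocol and a later model choice does not repair it. A SAP also cannot use a group code that was never attached to the data.

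**Baseline adjustment may restore the power.** This stands if d is on the raw SD scale. The protocol states d for the ANCOVA itself, and its sample size matches that reading, so it claims no such reserve. The scale is not settled by the text.

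**Readings that go too far.** A reader might infer that the error favours the new programme. The documents do not support this: the planned test is two-sided, and an understated standard error leaves the point estimate alone and raises false rejections in both directions. A reader might also assume that each group keeps one treatment team throughout. Only fixed membership is stated. Treating controls as unclustered is likewise an assumption, since they too are treated in groups, though mainly open ones.

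**Conclusion.** The point holds in conditional form. The sample size and the stated primary test assume independence, while the protocol itself prescribes closed-group delivery in one arm. For any positive ICC the standard error is understated, the two-sided type I error exceeds 5%, and power at d = 0.3, on the scale used in the calculation, is below 80%.

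The consequence is negligible near ICC 0.01 and material from about 0.05, where roughly 5 points of power are lost and the error rate is about 0.065. These sizes rest on about 6 analysed per group and clustering in the intervention arm only. One might conclude that the trial is definitely underpowered or needs more patients; the documents do not establish this, because neither the ICC nor the baseline-outcome correlation is given. Severity: should be fixed.

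**What to change.** 1. **Data.** Attach a therapy-group code to each intervention participant's pseudonymised record from the start, assigned by the centre.
2. **Primary analysis.** Keep the baseline-adjusted ANCOVA of the FFbH-R at 12 months and account for therapy group. A partially nested model (random intercept for group in the intervention arm only, with small-sample degrees of freedom) is one acceptable choice. Group-robust standard errors with a small-sample correction are another.
3. **Power.** Keep 588 participants and restate the power over an explicit range of ICC and baseline-outcome correlation, saying whether d = 0.3 is on the raw or the baseline-adjusted scale.

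The cost is one variable, one changed sentence on the model and a power statement given as a range, possibly somewhat less favourable. No extra patients are required.

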**Data acquisition, -keeping and -transfer.**

Potential participants in the control phase as well as in the intervention phase who met the inclusion criteria were identified and informed about the study by their rehabilitation physician during the medical interview at the beginning of the inpatient rehabilitation period. In the preparation phase, all employees of the participating rehabilitation centers will receive intensive training in respect of all procedures that are relevant to the recruitment process. Structural and process procedures for the use of the patient information and informed consent, distribution and collection of questionnaires as well as its sending to the study centre will be rehearsed and automated; the entire questionnaire survey will be done by the rehabilitation centres. The scientific research institutes (University of Erlangen, University of Würzburg) only receive anonymous data.

### 3. **Study related interventions** and all necessary deviations from the usual routine:

The interprofessional rehabilitation program shows formal and didactic deviations from the standard multidisciplinary orthopedic rehabilitation. The modules are carried out in fixed groups with eight to twelve participants within a comprehensive and consistent treatment approach. In each rehabilitation centre, the sessions of the six modules were distributed over 12 days during the inpatient rehabilitation period, which lasted on

average three week. By means of an intensive interprofessional biopsychosocial training for all health professions before the start of the program and regular team meetings during the rehabilitation process close exchange-/cooperation relations are promoted between the involved professions. Furthermore a modification of the weighting of single interventions and contents are achieved compared with the usual care. For example, standard exercise therapy often follows a biomedical approach to improve physical fitness. In contrast, the behavioral exercise therapy module within the interprofessional rehabilitation program is directed to improve positive exercise experiences, to reduce pain related cognitions, as well as to promote a physically active lifestyle. Furthermore, the training and practice of active coping strategies to improve self-management of chronic non-specific low back pain for a sustained healthy active lifestyle are important key components of the interprofessional rehabilitation.

The interprofessional rehabilitation program is carried out in a standardised form and in fixed groups, so that in comparison to the daily routine individual differences in the quality and quantity of the rehabilitation treatment hardly will occur. The interindividual variability is low.

4. Will the study be carried out according to the recommendations of the World Medical Association (Declaration of Helsinki, revised version on the 48th WMA General Assembly, Somerset West, Republic of South Africa, October 1996) Please indicate if any other evaluation options have been exhausted.

This study is conducted according to the recommendations of the World Medical Association (Declaration of Helsinki, revised version on the 52nd WMA General Assembly, Edinburgh, Scotland, October 2000), as well as to the Guidelines for good clinical practice (ICH). Information for the participants about aims, content and further key aspects of the study and their agreement on study participation will be included in the „informed consent“, a written document. Furthermore they are informed that participation in the study is voluntary, refusal to participate will involve no disadvantages or loss of benefits, the withdrawal of the study is possible at any time without loss of benefits, and the data processing is anonymous. According to the national data protection laws all personal data were treated as confidential and were used only for scientific purposes. Individual data (assignment lists, pseudonymisation) are not combined with the data set and remain within the participating rehabilitation centres; questionnaires are forwarded anonymously to the scientific research institutes (University of Erlangen, University of Würzburg). After finishing the study the assignment list will be deleted in order to anonymise the study data.

There is no alternative evaluation possibility!

5. Mode of the research project:

Is the research project a

- ☐ A diagnostic test?
- ☒ A therapeutic test?
- ☐ A compatibility test?
- ☐ A solely scientific experiment?

6. Legal foundations

- a) Is this study about an experiment designed to explore or detect clinical or pharmacological effects of medication or to identify side effects or to examine resorption, distribution, metabolism or excretion **with the aim to gain information about the harmlessness or effectiveness of the medication** (clinical testing of medication according to §§ 40 Medicines Act)?

**No, this is not the case!**

*Please give reasons. Explanations to the application form for evaluation of clinical medicine testing according to §§ 40 AMG can be found under the following link <http://www.ethik.med.uni-erlangen.de/AMG-Studien.htm>*

- b) Is this study about a clinical test according to §§ 20 Medizinproduktegesetz (Medicine product Act)?

☐ Yes ☒ No

*Please describe. Does a CE certification of the medical product exist? Are there any additional invasive or other straining experiments being carried out?*

- c) Does this study contain plans according to §§ 8 Gesetz zur Regelung des Transfusionswesens (German regulation of transfusion Act)?

☐ Yes ☒ No

7. Is this study about an experiment according to

|                                               |                              |                                        |
|-----------------------------------------------|------------------------------|----------------------------------------|
| §§ 23 of the German Radiation Protection Act? |  Yes |  No |
| §§ 28 of the German X-ray regulations?        |  Yes |  No |

*Please describe. In case the answer is yes: Will the necessary official expert's reports be obtained?*

8. Study type:

☒ Open  
☐ Blind  
☐ Doubleblind  
☒ Comparing  
☐ Randomised  
☒ Multicentric  
☒ Field study  
☐ Pilot study

9. **Scientific/academic rationale of the project, in particular:**

- a. Aims of the study

Based on a structured rehabilitation program with a biopsychosocial approach and an integrative linking of different treatment components, the major aim of the present study is to evaluate the long-term effectiveness of such an interprofessional rehabilitation program compared to the standard multidisciplinary orthopedic rehabilitation (usual care) to promote self-management (e.g. functional ability, quality of life, pain related cognitions) of chronic non-specific low back pain.

- b. Presentation of the current state of knowledge

International reviews recommend intensive multidisciplinary biopsychosocial rehabilitation in cases of disabling chronic non-specific low back pain (Guzmán et al. 2004, Hayden et al. 2005, Ostelo et al. 2005, van Tulder et al. 2003, Schonstein et al. 2003). In contrast, to date there are only few national intervention studies, that have evaluated the effectiveness of multidisciplinary biopsychosocial rehabilitation for the treatment of adults

with disabling chronic non-specific low back pain. Two uncontrolled studies with a pre-post design report several positive effects of outpatient multidisciplinary biopsychosocial rehabilitation in adults with chronic non-specific low back pain (Schöps et al. 2000, Pflingsten and Hildebrandt, 2001). Furthermore, two reviews summarise the currently available evidence for the effectiveness of multidisciplinary rehabilitation in Germany (Hüppe and Raspe 2003, 2005). In the mostly uncontrolled studies only short-term intervention effects (pre-post) are reported, usually with very low effect sizes. Hüppe and Raspe (2005) underline, that controlled studies which assess the mid- and long-term effects of a multidisciplinary rehabilitation compared to no treatment or usual care are lacking. Only one controlled study compared multidisciplinary biopsychosocial rehabilitation with multidisciplinary orthopedic rehabilitation in the German rehabilitation setting, and reported significant effects on function and pain after ten months in favour of the multidisciplinary biopsychosocial rehabilitation. Compared to a functional restoration approach with standard exercise therapy to improve physical fitness, especially resource-oriented knowledge and behavior modification, as well as to promote positive experiences with exercise seem to be important components to improve long-term effectiveness (e.g. Kleist et al. 2001). Further preliminary results of on-going studies which assess the effects of multidisciplinary biopsychosocial rehabilitation named „behavioral medical rehabilitation“ compared to standard multidisciplinary rehabilitation also point in this direction (Mehnert et al. 2007, Schwarz et al. 2007). Overall, the few so far existing monocentric studies indicate that the expenditure to implement an interprofessional rehabilitation program is feasible and promising. Nonetheless, the purposeful integrative linking of knowledge-, behavior- and activity-related interventions has not been established in clinical routine so far. The development of national disease management guidelines (KTL evaluations, Gülich et al. 2003) as well as formative evaluations of the health training concept of the German pension insurance (Worringen et al. 2006) imply quality and quantity deficits in the implementation of patient education in medical rehabilitation.

